### Sample size calculation

This study is designed as a proof-of-concept study with multiple outcomes of interest. We expect the effect size of imatinib treatment on the various parameters to be very high, since we specifically select patients who express high levels of the drug targets. However, we are aware of possible factors that may reduce the observed effect size. This includes intra-tumour heterogeneity in target expression – causing potential misclassification – and variation in drug distribution throughout the tumour and between patients. Therefore, we anticipate a medium to high Cohen effect size for the primary endpoint (i.e. Cohen’s effect size of 0.65). To demonstrate such an effect, we need to include 27 (evaluable) patients, based on a two-sided paired-samples t-test with a significance level α of 0.05 and power 1-β of 90%. We specifically chose this high power in order not to dismiss effects that are potentially relevant for further development of imatinib therapy in colorectal cancer patients. Given that approximately 25% of colon cancers are CMS4, at least 4*27 = 108 eligible patients with newly diagnosed colon cancer will need to be pre-screened with the RT-qPCR test. Since <10% of the patients undergoing colonoscopy are diagnosed with colon cancer, at least 1.100 patients will have to be approached for pre-screening informed consent.

### Statistical analyses

Imatinib-induced changes in the expression of specific gene signatures associated with CMS4 will be assessed by RNA-sequencing analysis. The signatures will be obtained from published literature and our own data. In addition, imatinib-induced gene expression changes will be analysed in a non-biased way by gene ontology and gene enrichment analyses. Using the appropriate statistical tests depending on distribution of the data (paired samples t-test in case of normal distribution or Wilcoxon signed-rank test if the distribution remains non-normal even after transformation) we will test whether there is a significant change in gene signature expression. Phosphorylation of PDGFRα/β and KIT will be quantitatively assessed as a fraction of the total amount of PDGFRα/β and KIT present in a sample. Post-treatment imatinib-induced inhibition of PDGFR phosphorylation will be compared relative to the pre-treatment sample (i.e. the patient’s internal control) using the appropriate statistical tests. Correlations between plasma trough levels and intratumoural concentration of imatinib, and between the extent of PDGFR and KIT inhibition and systemic/intratumoural imatinib concentrations will be evaluated using Pearson correlation coefficient. The Wilcoxon matched pairs signed rank test will be used to compare serial ctDNA and CEA levels. Organoid-forming potential of the tumours after imatinib therapy will be compared with the general success rate of organoid-establishment from colon cancers, using a Fisher exact test. In case of missing data, samples will be excluded pair-wise.

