## Methods

### Study design

The ImPACCT trial is an open-label, multi-centre proof-of-concept study. The primary endpoint of this trial is the effect of imatinib treatment on tumour biology, which is a pharmacodynamic endpoint, and as such this trial could be deemed a phase II/translational trial. A study flow chart is depicted in Fig. 1.

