### Objectives

The primary objective of this trial is to investigate the effects of treatment on pro-metastatic pathways in aggressive primary CMS4 tumours. RNA sequencing will be performed on pre- and post-treatment tissue samples to document imatinib-induced genome-wide gene expression changes.

Secondary objectives include: to assess the extent of inhibition of PDGFR- and KIT after imatinib treatment; to relate intra-tumoural imatinib pharmacokinetics (PK) to systemic imatinib concentrations; to relate the level of inhibition of PDGFR/KIT signalling and the extent of changes in gene expression to the systemic and intra-tumoural PK of imatinib and its active metabolite CGP74588; to assess changes in tumour markers during treatment by measuring the concentrations of plasma-CEA and circulating tumour DNA (ctDNA) and to study the effects of imatinib on organoid-forming potential. Finally, the effect of short-term exposure to imatinib immediately followed by bowel surgery on the complication rate will be monitored.

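### The 5% error rate and 90% power are computed for one paired test, but the primary endpoint is an unspecified number of gene signatures with none named as primary

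*Protocol article*

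**What the plan says.** **Sample size calculation (protocol article).** The sizing is for a single endpoint: "we anticipate a medium to high Cohen effect size for the primary endpoint (i.e. Cohen’s effect size of 0.65"). The number follows, "we need to include 27 (evaluable) patients", and it is "based on a two-sided paired-samples t-test with a significance level α of 0.05 and power 1-β of 90" per cent. The same paragraph acknowledges that the study has several outcomes of interest.

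**Study design and Objectives.** The endpoint to which these figures should attach is given in general terms only. Under Study design: "The primary endpoint of this trial is the effect of imatinib treatment on tumour biology". Under Objectives: "The primary objective of this trial is to investigate the effects of treatment on pro-metastatic pathways in aggressive primary CMS4 tumours". Neither section names a measured variable with a scale.

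**Statistical analyses.** The endpoint becomes measurable here, in the plural: "Imatinib-induced changes in the expression of specific gene signatures associated with CMS4 will be assessed by RNA-sequencing analysis". On their origin: "The signatures will be obtained from published literature and our own data". Ontology and enrichment analyses are added alongside. After a paired t-test or a Wilcoxon signed-rank test is chosen according to the distribution, "we will test whether there is a significant change in gene signature expression". The section gives no number of signatures, no lead signature, no composite score, no success rule and no significance level per signature. The only alpha in the article is the 0.05 in the sample size paragraph.

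**The concern.** A significance level and a power are properties of a specific test. The article states both for one test and then describes an open set of tests as the primary analysis. As the text stands, a reader cannot say which signature has a standardised change of 0.65, or which p-value is controlled at 5%.

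The consequence lies in how the result will be used. The Discussion presents proof of concept as a safeguard against moving drugs forward without foundation. It also says that the observed size of the effect on tumour biology can inform a larger randomised phase II trial. If the signature that carries the conclusion can be settled after the paired data are seen, the chance of a false claim may exceed 5%. An effect taken from the most favourable of several signatures would also tend to be too large for planning the next trial.

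**Working it through.** **Inputs from the article.** Standardised paired difference d = 0.65; two-sided alpha = 0.05; power 90%; n = 27; paired t-test (all from Sample size calculation).

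**Assumptions.** The article does not give the number of signatures k, so I take k = 3, 5 and 10. Correlation between signature changes is not given either; I take 0 (independence), 0.5 and 0.8.

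**Step 1: reproduce the plan's figure.** Power of a paired t-test comes from the noncentral t distribution with n − 1 degrees of freedom and noncentrality d√n.
- n = 27: noncentrality 0.65 × √27 = 3.38; power 90.2%.
- n = 26: power 89.0%.

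So 27 is the smallest n that reaches 90%, and the stated figure is correct for one test.

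**Step 2: false-positive chance if any one signature at 0.05 counted as success.** Under independence this is 1 − 0.95^k. For correlated signatures it was simulated with n = 27, equicorrelated normal differences and no true change (40,000 replicates).

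| k | Independent | Correlation 0.5 | Correlation 0.8 |
|---|---|---|---|
| 3 | 1 − 0.95³ = 14.3% | 12.7% | 10.1% |
| 5 | 1 − 0.95⁵ = 22.6% | 18.8% | 13.2% |
| 10 | 1 − 0.95¹⁰ = 40.1% | 29.3% | 17.6% |

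The signatures are all described as CMS4-associated, so the correlated columns are the more plausible ones.

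**Step 3: power for one given signature with Bonferroni.** Same noncentral t calculation at d = 0.65, with alpha replaced by 0.05/k.

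| k | Alpha per test | Power at n = 27 | n for 90% |
|---|---|---|---|
| 3 | 0.0167 | 78.7% | 35 |
| 5 | 0.01 | 72.1% | 39 |
| 10 | 0.005 | 62.3% | 44 |

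**Step 4: power for at least one signature with Bonferroni.** This is the counterpart of the rule in Step 2. It was simulated at n = 27, assuming that every signature truly shifts by 0.65.

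| k | Correlation 0.5 | Correlation 0.8 |
|---|---|---|
| 3 | about 95% | about 90% |
| 5 | about 96% | about 89% |
| 10 | about 97% | about 87% |

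At correlation 0.9 and k = 5 it is 84%. Steps 3 and 4 answer different questions, and the article does not say which one its 90% refers to.

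**The case against.** The strongest reply is that a journal article condenses. The list of signatures, the scoring formula, the date of freezing and any multiplicity rule may sit in the full protocol or analysis plan, neither of which is shown, and their absence here is no fault. That stands. What remains is a mismatch inside the article: it sizes one test on a singular endpoint and then measures that endpoint by several signatures.

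A reader might infer more than the text supports, in five respects.

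- **That each signature is tested at 5% and any one suffices.** The article states neither. A composite score, a lead signature or a requirement that all agree would fit the wording as well. The figures in Step 2 are therefore conditional.
- **That correcting for multiplicity must bring power well below 90%.** This is true for a given signature (Step 3). It is not true in general for at least one signature when all of them respond (Step 4).
- **That signatures will be trained on this trial's own samples.** The Background describes the group's earlier laboratory and expression work and its four-gene test, and the reference to own data reads naturally as that work. The article does not exclude trial samples, but nothing says they will be used.
- **That the endpoint's varying wording is a contradiction.** Study design gives the type of endpoint, Objectives the aim and Statistical analyses the measurement. They run from general to specific.
- **That the ontology and enrichment analyses add to the primary multiplicity.** They are introduced as an unguided addition beside the specific signatures.

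It is also fair to say that this is an open-label proof-of-concept study with no stated p-value rule for proceeding. That lowers the severity but does not tell the reader which test the 90% describes.

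**Conclusion.** The point holds as a mismatch between sizing and endpoint. The stated 5% and 90% belong to one paired test, and the article defines no single primary test to which they apply. The sample size arithmetic is correct.

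The size is conditional. With k assumed and an any-one rule that the article does not state, the false-positive chance would be roughly 10–14%, 13–23% and 18–40% for 3, 5 and 10 signatures. With Bonferroni, power for a given signature would be 79%, 72% and 62%, while power for at least one would remain about 87–97% if all shift by 0.65 at correlation 0.5–0.8. The documents do not support a flat claim that the trial's error rate is several times 5% or that it is underpowered. If the full protocol already names one primary signature, stating it resolves the point. Severity: should be fixed.

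**What to change.** Designate one CMS4/mesenchymal signature or one composite score as the sole primary endpoint, tested at two-sided 0.05. Freeze its gene list and scoring formula before any paired sequencing data are seen, and state that it was derived from data outside this trial. The 27 evaluable patients and 90% power then stand unchanged. Treat the remaining signatures and the ontology and enrichment analyses as secondary, with Holm or Benjamini-Hochberg adjustment.

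If several primary signatures are preferred, state how many, the success rule (any, all or a given one) and the adjustment, and restate the power under that rule. If the rule is Bonferroni with 90% power for a given signature, Step 3 shows 35, 39 or 44 patients for 3, 5 or 10 signatures.

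The first option costs wording only, with no added patients or assays. Its downside is that one signature must be chosen in advance and may prove not to be the one that responds most.

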## Abstract

**Background:**

The identification of four Consensus Molecular Subtypes (CMS1–4) of colorectal cancer forms a new paradigm for the design and evaluation of subtype-directed therapeutic strategies. The most aggressive subtype - CMS4 - has the highest chance of disease recurrence. Novel adjuvant therapies for patients with CMS4 tumours are therefore urgently needed. CMS4 tumours are characterized by expression of mesenchymal and stem-like genes. Previous pre-clinical work has shown that targeting Platelet-Derived Growth Factor Receptors (PDGFRs) and the related KIT receptor with imatinib is potentially effective against mesenchymal-type colon cancer. In the present study we aim to provide proof for the concept that imatinib can reduce the aggressive phenotype of primary CMS4 colon cancer.

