The pro-metastatic pathways that are upregulated in CMS4 provide opportunities for subtype-targeted therapy. CMS4 tumours are characterised by high expression of stem cell and mesenchymal genes, and a high stromal content [9]. We have previously shown that Platelet-Derived Growth Factor Receptors (PDGFRs) and KIT are highly expressed in mesenchymal-type colon tumours and that their expression strongly correlates with disease-free survival. Moreover, in vitro and in vivo inhibition of PDGFR and KIT tyrosine kinase signalling reduced invasiveness, metastatic potential and stem-like characteristics of mesenchymal-type colon cancer [10–12]. Based on these findings we hypothesise that patients with poor-prognosis mesenchymal-type colon cancers could benefit from treatment with imatinib, a tyrosine kinase inhibitor with high selectivity for PDGFR and KIT.

To test this hypothesis in a proof-of-concept study, we designed the ImPACCT trial (*Im*atinib as *P*re-operative *A*nti-*C*olon *C*ancer *T*argeted therapy). In ImPACCT, patients with CMS4 colon cancer are identified with a recently developed 4-gene RT-qPCR test that measures *PDGFRA, PDGFRB, PDGFC* and *KIT* expression levels in diagnostic tumour biopsies [13]. Pre-selected patients with CMS4 tumours are then treated with imatinib during the pre-operative window period (the time between initial cancer diagnosis and surgery). This allows comparison of pre-treatment diagnostic tumour biopsies with biopsies obtained from the resection specimen after treatment. The primary objective is to assess whether imatinib treatment reduces the aggressive phenotype of CMS4 tumours in colon cancer patients. ImPACCT may not only form the basis for future adjuvant studies with imatinib, but could also serve as a blueprint for other proof-of-concept studies with subtype-targeted therapies.

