### Study population

All patients who are scheduled for a diagnostic colonoscopy on account of clinical suspicion of colon carcinoma will be approached for permission to obtain extra biopsies for this study in case a tumour is found in the colon. These biopsies are pre-screened with the new RT-qPCR test that predicts the chance of a tumour being CMS4, based on the combined expression of imatinib targets *PDGFRA, PDGFRB, PDGFC* and *KIT* [13]. If the predicted chance of CMS4 in the biopsies is 50% or higher, patients will be approached for imatinib therapy. The study population that undergoes treatment with imatinib will thus consist of treatment-naïve newly diagnosed colon cancer patients with a tumour with a high probability of having the CMS4 phenotype. In- and exclusion criteria for enrolment in the second part of the trial (imatinib therapy) are listed in Table 1.

**Table 1 Tab1:** In- and exclusion criteria for treatment with imatinib

Inclusion criteria	Exclusion criteria

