- Male or female aged ≥18 years; - Histologically proven adenocarcinoma of the colon; - Completed cancer staging with CT-abdomen and CT-thorax/X-thorax according to hospital’s standard of care; - Confirmed eligibility for surgery with curative intent as deemed by the hospital’s multidisciplinary board review; - Test positive for CMS4 subtype; - ≥4 properly stored pre-treatment biopsies for gene expression analysis/ELISA; - WHO performance status 0 or 1; - Adequate haematology status and organ function (defined as: normal creatinine clearance (≥60 ml/min (MDRD)), ALAT within 2.5× upper limit of normal (ULN), PT-INR < 1.5, leukocytes >1,5*10^9/L, Hb > 6.0 mmol/L, platelets >100*10^9/L); - Willingness and ability to comply with scheduled visits, treatment plans and laboratory tests; - Provision of written informed consent.	- The presence of synchronous distant metastases; - Current hospital standard of care dictates that subject should undergo any neoadjuvant therapy; - Concurrent participation in another clinical trial using any medicinal product, or participation in such a trial in the period of three months prior to the current trial; - Women who are pregnant, plan to become pregnant or are lactating during the study or for up to 30 days after the last dose of imatinib; - Known HIV or Hepatitis B/C infection; - Known symptomatic congestive heart failure; - Co-morbidity requiring concomitant treatment with drugs that act as strong inducers of CYP3A4 or with drugs with a narrow therapeutic range influenced by imatinib.

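### The organoid endpoint compares imatinib-treated tumours selected as CMS4 with colon cancers in general, so the result cannot be attributed to imatinib unless both subtypes establish equally often untreated

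*Protocol article*

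**What the plan says.** Under Objectives, one secondary aim is "to study the effects of imatinib on organoid-forming potential". Under Statistical analyses, the only test given for that aim is that tumours after imatinib "will be compared with the general success rate of organoid-establishment from colon cancers, using a Fisher exact test".

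The treated group is not a general one. Under Study population: "If the predicted chance of CMS4 in the biopsies is 50% or higher, patients will be approached for imatinib therapy". Under Sample size calculation, the share of this subtype in the wider population is given: "Given that approximately 25% of colon cancers are CMS4". The Background says why the subtype is of interest: "CMS4 tumours are characterised by high expression of stem cell and mesenchymal genes, and a high stromal content".

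The article describes no untreated arm, no CMS4-matched organoid series and no organoid culture from pre-treatment tissue. The inclusion criterion on stored biopsies reads "≥4 properly stored pre-treatment biopsies for gene expression analysis/ELISA" and does not mention organoid culture.

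**The concern.** The objective concerns a drug effect, but the comparison changes two things at once. One side is treated and selected as probable CMS4; the other is untreated and, on the plain reading of the text, covers all colon cancers.

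If untreated CMS4 tumours establish less often than others, an inert drug can appear to lower organoid formation. If they establish more often, a real reduction can bring treated tumours down to the general rate and go unseen. The readout could mislead either way, and a reader could not tell which had happened.

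The other treatment-effect tests in the same section do not share this weakness. Gene signatures, receptor phosphorylation, ctDNA and CEA are all compared within the patient, before against after treatment. Only the organoid test relies on an external reference that is not matched for subtype.

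**Working it through.** **The plan's own figure.** The article gives no numbers for the organoid comparison. Its one sample size is for the primary endpoint: 27 evaluable patients, two-sided paired t-test, effect size 0.65, alpha 0.05, power 90%. From the noncentral t distribution with noncentrality 0.65 × √n, power is 0.890 at n = 26 and 0.9015 at n = 27. So 27 reproduces, and nothing below bears on it.

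**Inputs from the article.** Up to 27 treated tumours; selection at a predicted CMS4 chance of 50% or more; CMS4 share about 25%, hence 100% − 25% = 75% non-CMS4 in a general series; Fisher's exact test.

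**Assumptions of this review.** All organoid success rates; a reference series of 100 (or 50) tumours; an attempted culture from all 27 treated tumours; rejection at two-sided p ≤ 0.05. The rate called CMS4 below stands for tumours passing the RT-qPCR rule, although some of these may not be truly CMS4.

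**Method.** Let p4 be the untreated success rate of selected tumours and g the general rate. With no drug effect, treated successes follow Binomial(27, p4) and reference successes Binomial(n, g). The rejection probability is the sum of the products of the two binomial probabilities over all outcome pairs for which Fisher's p is at most 0.05.

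**Check 1: no drug effect, g = 60%.** The non-CMS4 rate implied by the 25/75 mix is (0.60 − 0.25 × p4) / 0.75.

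| p4 | Implied non-CMS4 rate | Rejection, 100 reference tumours | Direction |
|---|---|---|---|
| 60% | 60.0% | 4.2% | both |
| 50% | 63.3% | 13.8% | almost all towards worse establishment |
| 40% | 66.7% | 42.3% | worse |
| 80% | 53.3% | 46.8% | better |

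With equal subtype rates the test keeps its level. As the rates separate, it rejects because of subtype alone. With 50 reference tumours, the 50% row falls to about 10%.

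**Check 2: a true reduction, 100 reference tumours.** Suppose imatinib lowers CMS4 success from 90% to 60%, and non-CMS4 success is 60%. The general rate is 0.25 × 0.90 + 0.75 × 0.60 = 0.675. A significant reduction is then found in 9.6% of trials against the general rate, compared with 91.1% against untreated CMS4 tumours. For a fall from 80% to 50% with non-CMS4 at 50%, the general rate is 0.25 × 0.80 + 0.75 × 0.50 = 0.575, and the chances are 8.8% and 83.1%.

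So under assumed but coherent rates, the same comparison can produce a false signal or hide a large true one.

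**The case against.** The strongest reply is that the bias is unproven. The article gives no organoid success rate for any subtype, and if the rates are equal the planned test is valid, as the 4.2% row shows. This stands, and it rules out the stronger reading that the test can never show a drug effect.

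Second, the direction is open. If stem-like biology helps organoids to establish, the general rate understates what untreated CMS4 tumours would do. A significant reduction after imatinib would then be all the more convincing, and the price would be lost power. High stromal content might work the other way. This also stands: a false claim of benefit is only one of the possible errors.

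Third, the magnitudes rest on assumptions. Higher rejection rates can be produced, for example 77.3% at p4 = 30%, but that needs an implied non-CMS4 rate of 70%, a 40-point gap between subtypes. Such a figure should not be read as an expected error rate.

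A reader might also infer that Fisher's test is the wrong test because a general rate is one fixed number. The text does not say the rate will be used that way. Naming Fisher's test suggests counts in two groups, and a condensed article may leave that detail to the full protocol.

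Finally, this is one secondary objective of a proof-of-concept study. That limits the consequence but does not remove the point: a formal test is stated for an aim worded as an effect of imatinib.

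**Conclusion.** The point holds as a limit on interpretation. The stated comparison confounds CMS4 selection with treatment. Attributing the result to imatinib needs equal untreated establishment rates in CMS4 and non-CMS4 tumours, which the protocol does not state and its own account of CMS4 makes doubtful.

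The direction and size of the bias cannot be determined from the document. The rejection rates above are illustrations that depend on the assumed success rates and reference size. They show that a modest gap matters somewhat and a wide one matters a great deal, but not which applies here.

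The documents do not support saying that the test is invalid in itself, that Fisher's test is the wrong choice, or that the trial's main conclusion is at risk. The primary gene-expression endpoint and N = 27 are untouched.

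**What to change.** In Statistical analyses, replace the general success rate with a reference restricted to untreated colon tumours that meet the same RT-qPCR rule (predicted CMS4 chance at least 50%) and are cultured by the same procedure. This applies where such a series exists with tissue or expression data on which the rule can be run. Fisher's exact test on the two sets of counts can then stay.

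If no such series exists, report the proportion of treated tumours that establish organoids with an exact 95% confidence interval, label it descriptive, and make no claim of an imatinib effect.

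The second option costs only a change of wording. The first may need the 4-gene test on stored samples and leaves a smaller, less precise reference group. The article does not show that suitable stored tissue from earlier organoid attempts is available, so the sponsor should confirm this before choosing.
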